#### Prevention of Mother-to-Child Transmission of HIV Appointment Attendance

We will measure the proportion of mothers who attended all scheduled ANC appointments, documenting late (>7 days past scheduled date) and missing (>14 days past scheduled date) attendance. The number of possible appointments will vary on gestational age at PMTCT enrollment; thus we will measure the median number of visits, the proportion who received the recommended 4 or more appointments, and the proportion enrolled by the recommended 14 weeks gestation.

#### Viral Load Suppression

We will document the proportion of pregnant women who had a VL sample collected during pregnancy: 6 months after ART initiation for those diagnosed during ANC or within the past 6 months for those already established on ART, in accordance with national guidelines. We will abstract data on VL from the HITSystem 2.0 (intervention) and the patient file and laboratory records (control) to assess the proportion with VL tests taken, the turn-around time (TAT) for return of results, and the proportion with suppressed VL results (defined as<1000 viral copies/ml) during pregnancy.

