Using chi-square tests, we will compare the proportion of pregnant women (1) attending all scheduled PMTCT appointments (4 or more PMTCT visits and late or missed visits), (2) tested for VL (VL sample collected, results returned, and detectible VL values), (3) delivery at the hospital, (4) enrolling in EID (dried blood spot sample collected by <7 weeks), and (5) have an infant diagnosed with HIV, between intervention and control sites. The median number of PMTCT appointments, median gestational week at first PMTCT appointment, and median TAT for VL results will be calculated and compared using Mann Whitney *U* tests. Although medication adherence documentation at the control site (typically described as poor, fair, or good) will not permit direct comparison, the proportion of pregnant women at the intervention site with >95% adherence will be described. Participant preferences for the content and frequency of SMS text messages for medication adherence support will also be described. *P* values will be adjusted (using Tukey correction) for multiple tests, where appropriate. Quantitative data will be analyzed using Statistical Application Software (SAS) version 9.4.

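### The viral load testing comparison keeps women in the denominator whose sample cannot fall due before delivery, and the viral load category analysed does not match the outcome defined

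*Protocol article*

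**What the plan says.** The Viral Load Suppression section sets the outcome: "We will document the proportion of pregnant women who had a VL sample collected during pregnancy". It gives two timings: "6 months after ART initiation for those diagnosed during ANC", or "within the past 6 months for those already established on ART". It then lists VL tests taken, turnaround time, and "the proportion with suppressed VL results (defined as<1000 viral copies/ml) during pregnancy".

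The Statistical Analyses section gives the test: "Using chi-square tests, we will compare the proportion of pregnant women", with one of the listed items being "VL sample collected, results returned, and detectible VL values". It names no covariates and no restriction to women whose sample is due.

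Three other places bear on who is counted:

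- Participant Eligibility sets no gestational-age limit.
- The intervention specifications admit both previously diagnosed women and women newly diagnosed at antenatal screening.
- The appointment attendance outcome includes "the proportion enrolled by the recommended 14 weeks gestation", so some entry after week 14 is expected.

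**The concern.** Six months is about 26 weeks, and a pregnancy lasts about 40. A newly diagnosed woman who starts ART in mid-pregnancy delivers before the sample is due. On the text as written she counts as not tested, however well the hospital follows the schedule. The article makes an allowance of this kind for visits, where it notes that the possible number depends on gestational age at enrolment, but makes none for VL.

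The measured proportion therefore has a ceiling set by who walks in, not only by care. The ceiling could hide a real improvement in VL testing or, if the two hospitals see different women, suggest one that is not there. The Discussion says the findings will refine how antenatal VL results are tracked and used ahead of a larger efficacy trial, so a misread pilot result would carry forward.

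A separate problem is that the VL result named for testing is not the one defined as the outcome.

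**Working it through.** **The plan's own figure.** No rate, sample size or power is stated for VL. The only design figure is for the primary outcome: 47% vs 20%, 80% power, two-sided alpha .05. The two-proportion formula gives 47 per arm without continuity correction and 54 with it, so the stated 54 per hospital reproduces and is used below.

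**Step 1: latest feasible ART start.** Latest start = gestation at delivery − 26.1 weeks.

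- Delivery at 37 weeks: 37 − 26.1 = 10.9 weeks
- Delivery at 40 weeks: 40 − 26.1 = 13.9 weeks
- Delivery at 42 weeks: 42 − 26.1 = 15.9 weeks

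**Step 2: ceiling on the proportion tested.** Let f be the share of women newly diagnosed and e the share of those who start ART early enough. The highest attainable proportion is 1 − f(1 − e). The documents give neither f nor e, so all values here are assumptions. With e = 0.2:

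- f = 0.2: 1 − 0.2 × 0.8 = 84%
- f = 0.4: 1 − 0.4 × 0.8 = 68%
- f = 0.6: 1 − 0.6 × 0.8 = 52%

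If only women whose sample falls due before delivery are counted, the ceiling is 100% at both hospitals.

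**Step 3: identical care.** Assume q = 80% collection among women able to have the sample, at both hospitals. Expected proportion = q × [1 − f(1 − e)], with e = 0.2. The last column is the exact rejection probability of the Pearson chi-square test at 54 per arm.

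| Newly diagnosed, A vs B | Expected tested, A vs B | Gap (points) | Rejects |
|---|---|---|---|
| 40% vs 40% | 54.4% vs 54.4% | 0 | 4.5% |
| 35% vs 45% | 57.6% vs 51.2% | 6.4 | 9.3% |
| 30% vs 50% | 60.8% vs 48.0% | 12.8 | 25% |

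For the last row: 0.8 × (1 − 0.30 × 0.8) = 0.608 and 0.8 × (1 − 0.50 × 0.8) = 0.480.

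**Step 4: equal mix, a real difference in care.** Suppose collection among able women is truly 60% vs 85%. With f = 0.4 and e = 0.2 the multiplier is 0.68, so the proportions become 40.8% vs 57.8%. The 25-point difference shrinks to 17. At 54 per arm, power falls from 84% (f = 0) to 40%. Restricting the denominator restores the 25-point difference, but in fewer women, so not all of that power returns.

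**Step 5: outcome and analysis side by side.** The outcome section gives one definition, below 1000 copies/ml. The analysis section names detectable values and gives no threshold. A value of 500 copies/ml meets the suppression definition and could also be called detectable, so the two descriptions can classify the same woman differently.

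**Step 6: women already on ART.** A sample counted as "within the past 6 months for those already established on ART" can predate the pregnancy, yet the outcome requires collection during pregnancy. The two conditions do not agree.

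**The case against.** - **Covariate control.** Statistical Analyses says analytic models will control for baseline covariates that differ significantly and for gestational age where it affects the services a woman is eligible for. VL testing is such a service, so the authors foresaw the issue. But the VL items are assigned to chi-square tests, which take no covariates, and gestational age alone does not show who is due without ART status at entry. Waiting for a significant imbalance is also a weak safeguard: at 54 per arm, a true 30% vs 50% difference in newly diagnosed share reaches p < .05 only about 57% of the time.
- **Comparable hospitals.** Trial Design describes hospitals with comparable basic patient characteristics, and the article compares median gestational week at first appointment, so late entry at one site would be visible. This stands, and it is why a false difference cannot be asserted. One hospital per arm, with a phone requirement at the intervention site only, makes imbalance plausible and no more.
- **Denominators left to a fuller document.** The article refers to national guidelines and lists tests taken without repeating the timing condition, so an earlier sample might count. That softens the impossibility, but a hospital keeping exactly to the stated timing would still record these women as untested. If suppression is taken among women with results, women without a sample do not enter it; the denominator problem concerns testing.
- **Importance.** This is one secondary outcome in a pilot, and the article concedes that VL is not consistently collected in pregnancy. That limits the weight of the point.

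**Conclusion.** The point holds in a limited form. As written, the testing proportion includes newly diagnosed women who start ART after about week 14 (about 11 to 16, depending on delivery) and cannot meet the stated timing. Under equal case mix the consequence is dilution only. Under unequal mix a false gap is possible: about 6 to 13 points for the assumed shares in Step 3. All these sizes rest on assumed values of f, e and q.

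A reader might infer that the comparison reflects case mix rather than care. The documents do not support that: the same rule applies at both hospitals, and no imbalance is shown. A reader might also infer that suppression is defined by two cut-offs. It is defined once; the analysis uses a mismatched term without a threshold, and that mismatch causes no case-mix bias. Nor is VL the only biological outcome compared, since infant HIV diagnosis is compared as well. The primary outcome and its sample size are untouched.

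**What to change.** 1. For the comparison of VL testing, count only women whose guideline VL falls due before their own delivery, using actual ART start and delivery dates rather than a fixed 14-week cut-off.
2. Report the number not due, by hospital and by ART status at entry.
3. Report suppression among women with a result.
4. Use the below-1000 copies/ml definition in both sections, in place of the detectable category.
5. Reconcile the six-month look-back for women already on ART with the requirement that the sample be collected during pregnancy.

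This takes a few sentences in the analysis plan and changes nothing in care. It needs ART start and delivery dates, which the planned record review should already supply. The cost is a smaller denominator, and so less precision, for this secondary outcome.

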#### Medication Adherence

As VL is still not consistently collected during pregnancy, we will rely on other indicators of adherence including self-report of missed doses in the 7 days before appointment (prescribed vs taken) and pill counts conducted by relevant providers (dispensed vs returned). Adherence data will be entered in the HITSystem 2.0 at each appointment. We will calculate the proportion of patients who report >95% adherence to doses prescribed (7-day self-report) and pill count.

*Hospital delivery* will be estimated from the proportion of pregnant mothers who deliver at a health facility. Women who do not deliver at the study hospital will be contacted within 2 weeks of their estimated due date to check on their progress, document location of birth, and encourage prompt return to the facility for postpartum and postnatal care. *EID enrollment* will be measured using the proportion of HIV-exposed infants tested by 6 weeks of age (<7 weeks).

*Infant and maternal mortality* will be reported separately, noting all available data on date and cause of death. A future study will utilize a design with a longer follow-up period and larger sample size to adequately evaluate perinatal transmission of HIV.

#### Power and Sample Size

The required sample size was calculated to compare differences in proportions of complete PMTCT retention for the intervention (p1) and control (p2). We estimated complete retention by combining available retention data from Kenya for each phase: antenatal retention (68%) [19], hospital-based deliveries (61%) [36], and postnatal retention for HIV-exposed infants within 12 weeks (54.9% [21] to 80.7% [20]; average 67%). Recognizing that these estimates do not represent cumulative risk for the same individuals, we conservatively estimate complete PMTCT at the control site to be 20%. Our EID pilot data showed that retention doubled at 9 months with retention rates as high as 94.2% [33]. Using a midrange between differences achieved from published studies and our own pilot study, we conservatively estimate complete retention of 47% for HITSystem 2.0 participants. A sample size of 108 (54 intervention and 54 control participants) is needed to achieve 80% power to detect a significant difference in the proportion of complete PMTCT retention with chi-square tests (goodness of fit test: contingency table) with an effect size of 0.27 and a 2-tailed alpha of .05. Accounting for the proportion with mobile phone utilization, and 1.5% maternal mortality [45] and 3.7% [46] perinatal mortality, we estimate n=70 eligible participants. During Phase 3 enrollment, we plan to enroll n=54 of the n=70 eligible PMTCT patients per hospital. On the basis of our initial HITSystem pilot where <1% of women declined, we anticipate high participation.

#### Statistical Analyses

To examine the baseline participant and facility characteristics, we will calculate descriptive statistics including proportions for categorical variables and means (SD) or median (interquartile range) for continuous variables [47]. For the primary outcome, chi-square tests will be used to compare the proportion with complete PMTCT retention between groups [48]. We will explore correlations between complete PMTCT retention and possible predictors (eg, knowledge, motivation to complete care, maternal HIV disclosure, perceived benefit of ART, maternal depression, and risk of intimate partner violence) using Phi, point-biserial, or Spearman rho statistics depending on the measurement level of each predictor [49]. Analytic models will control for significantly different preintervention covariates across conditions and hospitals, clustered observations (eg, time nested within setting), and gestational age as it impacts the eligible/recommended number of appointments or services.

For secondary analyses, Kaplan-Meier curves will illustrate differences in the duration of PMTCT retention before, during, and after delivery, accounting for the woman’s eligible period of engagement (based on the timing of enrollment and accounting for premature infant or maternal mortality). We will then identify time periods when meaningful decreases in PMTCT retention occur, using Cox proportional-hazard regression for survival analyses (ie, retention), if all assumptions are met [50]. Known variables associated with HIV service retention (age, disclosure status, educational level, and number of children [22,51,52]) and those correlated (*P*<.10) will then be included in a generalized linear mixed model to identify a parsimonious list of predictors.

Using chi-square tests, we will compare the proportion of pregnant women (1) attending all scheduled PMTCT appointments (4 or more PMTCT visits and late or missed visits), (2) tested for VL (VL sample collected, results returned, and detectible VL values), (3) delivery at the hospital, (4) enrolling in EID (dried blood spot sample collected by <7 weeks), and (5) have an infant diagnosed with HIV, between intervention and control sites. The median number of PMTCT appointments, median gestational week at first PMTCT appointment, and median TAT for VL results will be calculated and compared using Mann Whitney *U* tests. Although medication adherence documentation at the control site (typically described as poor, fair, or good) will not permit direct comparison, the proportion of pregnant women at the intervention site with >95% adherence will be described. Participant preferences for the content and frequency of SMS text messages for medication adherence support will also be described. *P* values will be adjusted (using Tukey correction) for multiple tests, where appropriate. Quantitative data will be analyzed using Statistical Application Software (SAS) version 9.4.

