### Phase 3: Trial Intervention

#### Trial Design

We will employ a matched, randomized pilot study design in 2 government hospitals with comparable resources, patient volume, and basic patient characteristics. One hospital will be randomized to receive the HITSystem 2.0 intervention and the other hospital will maintain standard of care PMTCT services. An extended 18-month implementation period will allow 9 months to reach the sample size requirement of n=54 at each hospital and another 9 months to ensure complete prospective outcome data from the first PMTCT appointment in pregnancy until the infant’s first HIV DNA PCR test result is determined. This follow-up period will assess complete retention throughout PMTCT services, ART adherence, and rates of infant HIV transmission. We will also collect retrospective PMTCT outcome data from each hospital for the 18 months before implementation to facilitate pre- and postcomparisons at the same facility.

Satisfaction interviews with HITSystem 2.0 users (HIV positive women and providers) will inform barriers to use that can be targeted either through future strategic refinement of the design or collaboration with key partners to address constraints beyond the scope of this intervention.

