##### Training of Hospital and Study Staff

Key hospital personnel (PMTCT and maternity nurses and mentor mothers) will be trained by employing hands-on data entry scenarios tailored to the specific capacity in which they will utilize the HITSystem 2.0. During the first weeks of implementation, the trained research assistant (RA) will work closely to ensure thorough understanding and accurate independent use of the HITSystem 2.0 and will be available throughout the study to retrain or assist in system-related problem solving. The RA will be based in the MCH department with PMTCT providers to monitor and support fidelity to intervention implementation and timely data entry into the HITSystem 2.0. The US-based HITSystem team will remotely review the entered data to identify any challenges or systematic errors to be addressed. This is the same training and implementation process successfully employed for the HITSystem pilot [33] and cluster randomized trial to evaluate EID outcomes [32]. Training at the control site will be limited to assessing participant eligibility, conducting informed consent, and administering the baseline survey. Nurses and mentor mothers directly involved in PMTCT service provision will conduct these research tasks. All research and clinical staff involved in the study will be trained on procedures to ensure participant confidentiality and secure data storage.

*Baseline surveys* will be conducted at the initial PMTCT enrollment visit at both intervention and control sites for all eligible women. In addition to the basic demographic information captured in routine care at both hospitals (age and number of children), questions will assess (1) knowledge and perceived importance of attendance at scheduled appointments; ART before, during, and after delivery; consequences of poor adherence; and infant testing, (2) motivation and self-efficacy to complete the targeted behaviors (eg, attendance, medication adherence, plan for delivery, and prompt EID enrollment) using scaled and Likert responses, (3) assessment of depression symptoms (6 questions to assess frequency of symptoms between 0 to 7 days a week) and risk for intimate partner violence (3 screening questions to facilitate counseling referral), and (4) male partner involvement. Study staff will enter completed paper surveys in Excel 2016 (version 1708).

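### The correlation screen for predictors of complete retention carries no hospital term, so a between-hospital difference in a predictor can raise or lower its chance of passing P<.10

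*Protocol article*

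**What the plan says.** The protocol article, Statistical Analyses, sets out the predictor work in steps.

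- The screen: "We will explore correlations between complete PMTCT retention and possible predictors", with knowledge, motivation, disclosure, perceived benefit of ART, depression and partner-violence risk as examples. The statistics are chosen "using Phi, point-biserial, or Spearman rho statistics depending on the measurement level of each predictor".
- The next sentence concerns models: "Analytic models will control for significantly different preintervention covariates across conditions and hospitals, clustered observations", and gestational age.
- In the following paragraph, two groups of variables go forward. The first is "Known variables associated with HIV service retention (age, disclosure status, educational level, and number of children"); the second is those correlated at P<.10. Both "will then be included in a generalized linear mixed model to identify a parsimonious list of predictors".

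The text does not say whether the correlations are taken over all women, by hospital or partialled for hospital. It describes one coefficient per predictor and one P<.10 list, so a single pooled coefficient is the natural reading.

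Three other places matter. Trial Design makes hospital and arm the same thing: "One hospital will be randomized to receive the HITSystem 2.0 intervention and the other hospital will maintain standard of care PMTCT services". The baseline survey that supplies most candidate predictors "will be conducted at the initial PMTCT enrollment visit at both intervention and control sites for all eligible women". Power and Sample Size puts control retention at 20% and then says "we conservatively estimate complete retention of 47% for HITSystem 2.0 participants".

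**The concern.** The question is whether a woman's knowledge, motivation, depression score and so on predict her complete retention. A coefficient over both hospitals tests something else: whether predictor and retention are correlated in the combined sample. Arm is one hospital each and is planned to shift retention by 27 percentage points, so the combined correlation contains a between-hospital part as well as the within-hospital part of interest.

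The between-hospital part acts in both directions. A variable unrelated to retention can pass because its mean is higher, or lower, at the intervention hospital. A variable that does predict retention can fail because its mean is less favourable there and the two parts cancel. At stake are the reported correlations and the nomination of survey variables for the predictor model.

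**Working it through.** **Inputs from the document.** 54 women per hospital; retention 47% (intervention) and 20% (control); screening threshold P<.10.

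**Assumed inputs.** The document gives no predictor means or effects. I therefore varied the between-hospital difference *d* from 0 to 1 SD and took a within-hospital log-odds slope of 0 (null predictor) or 0.6 per SD (odds ratio e^0.6 = 1.82). I read the P<.10 criterion as referring to the correlations with complete retention.

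**The plan's own figure first.** With p̄ = 0.335:

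n = [1.96·√(2·0.335·0.665) + 0.8416·√(0.47·0.53 + 0.20·0.80)]² / 0.27² = (1.308 + 0.538)² / 0.0729 ≈ 46.8, that is 47 per arm.

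The continuity correction gives (46.8/4)·[1 + √(1 + 4/(46.8·0.27))]² ≈ 53.9, that is 54 per arm and 108 in total. The stated sample size reproduces.

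**How much correlation arm alone creates.** For a predictor with no within-hospital relation to retention, the pooled correlation is the product of two parts:

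- arm with retention: 0.5·(0.47 − 0.20) / √(0.335·0.665) = 0.286
- arm with predictor: d / √(d² + 4)

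This gives 0.036 at d = 0.25, 0.069 at 0.5, 0.100 at 0.75 and 0.128 at 1.0. With 108 women (106 df), |r| must exceed about 0.159 for P<.10. The artefact alone does not reach the threshold, but it moves the sampling distribution towards it.

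**Pass rates at P<.10.** Simulation, 20,000 replicates per scenario, normal predictor. The within-hospital version is the same test after centring predictor and outcome in each hospital. For the real predictor, *d* is a deficit at the intervention hospital.

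| d (SD) | Null, pooled | Null, within hospital | Real (OR 1.8), pooled | Real, within hospital |
|---|---|---|---|---|
| 0 | 10% | 10% | 82% | 85% |
| 0.25 | 12% | 10% | 70% | 85% |
| 0.5 | 19% | 10% | 52% | 85% |
| 0.75 | 28% | 10% | 37% | 85% |
| 1.0 | 38% | 10% | 23% | 85% |

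A weaker real predictor (odds ratio 1.7 per SD) shows the same pattern: 74%, 59%, 42%, 28% and 17% pooled, against about 77% within hospital.

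**Binary predictor, no within-hospital relation (Phi).** The pooled pass rate is 16% at prevalences of 60% vs 40%, 23% at 70% vs 40%, and 33% at 70% vs 30%.

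**Boundary case.** If retention is 20% at both hospitals, the null pass rate is 10% at d = 0, 0.5 and 1.0. A mean difference does no harm unless retention also differs.

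**Second route into the model.** Suppose the mixed model is one of the analytic models that control for significantly different covariates, and take significant to mean P<.05 (an assumption). The real predictor above then enters either by the screen or as an adjuster in about 81% of trials at 0.25 SD and 91% or more from 0.5 SD upward.

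**The case against.** The strongest objection is that the section already deals with this. A reader might infer from the screen that a variable wrongly dropped is lost for good. The document does not support that. A wrong exclusion of this kind needs a baseline difference between hospitals, and variables with significant differences are the ones the models are said to control for. On the natural reading that the mixed model is covered, entry stays at about 80% or higher. Age, disclosure status, education and number of children enter whatever the screen shows. A wrong pass only nominates a variable, and a model that accounts for hospital can remove it.

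Most of this stands. Two things remain. The control sentence speaks of models, so the correlations themselves, which are results in their own right, stay distorted. Entry as an adjustment covariate is also an accidental repair: the text does not say that such a variable then counts as a candidate for the predictor list.

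It can also be said that the word pooled is nowhere used, and that stratifying exploratory coefficients is a detail an analysis plan may settle. That is fair as to silence, but the statistics named have no hospital term, so following the text as written produces the problem.

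Finally, the hospitals are matched on basic patient characteristics and no predictor means are given, so large differences cannot be called likely. The document does give one reason for some difference: under Participant Eligibility, phone access is required only at the intervention site.

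**Conclusion.** The point holds as a low-severity improvement to an exploratory step. Followed as written, the screen mixes the hospital difference into each predictor's correlation with retention. At assumed differences of 0.25, 0.5 and 0.75 SD, the null pass rate rises from 10% to 12%, 19% and 28%, and the pass rate for a real predictor that is lower at the intervention hospital falls from about 85% to 70%, 52% and 37%.

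These sizes rest on the planned 47% vs 20%, on the assumed shifts and slope, and on reading the coefficients as pooled. False passes are close to nominal near 0.25 SD.

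A reader might go further and conclude that the final predictor list will be wrong, or that the trial's main result is affected. Neither is supported. The figures describe the screen, not the error rate of the final model, which the document does not specify closely enough to compute. The primary chi-square comparison and the sample size do not depend on this step.

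**What to change.** State in Statistical Analyses that the screening associations are computed within hospital: partial point-biserial or Spearman correlations given site, and Mantel-Haenszel tests stratified by site for binary predictors. Apply the P<.10 rule to those results, and keep hospital as a fixed term in the predictor model that follows.

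The cost is one or two sentences and one degree of freedom per test, with no new data. In the scenarios above it loses no power even when the hospitals do not differ on the predictor (85% against 82% at d = 0). The Results section reports that no comparison of outcomes between the sites had been run, so at that stage the change could still be prespecified.
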